### Mediational Analyses

Cross-lagged panel designs will be pursued to make inferences about the temporal priority of a set of measures assessed longitudinally [85-87]. Accordingly, cross-lagged panel models permit the opportunity to determine the temporal precedence of antecedents and consequents in the set of constructs [86]: infant sleep quality, maternal sleep quality, and postpartum depression. The depiction of the proposed cross-lagged panel model to be tested is shown in Figure 2.

**Figure 2 figure2:**
[figure not shown]
Cross-lagged panel model. For diagrammatic clarity, not displayed but will be estimated as part of the model are the constructs for postpartum months 3 (T4), 4 (T5), and 5 (T6), the correlations across constructs in every measurement round, and predictive error terms.

The cross-lagged panel model findings in the above model are expected to help inform how to specify the mediational model for hypothesis 2b. We propose that the cross-lagged panel model will evidence the following significant temporal cross-lagged directions that are consistent with hypothesis 2b: SB versus TB→infant sleep→maternal sleep→postpartum depression. Thus, a longitudinal mediational model, incorporating the intervention factor, will be specified and estimated (Figure 3). This mediational model tests and proposes that following underlying mechanism: SB group (vs the control group) will improve infant sleep quality, which would then predict better maternal sleep quality and finally contribute to lower maternal postpartum depression. All the outcomes of aim 1 are incorporated into the aim 2 mediational model to provide comprehensive and compelling insights that will statistically connect all the psychosocial constructs and understand the underlying process of this RCT.

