Determine whether the use of a smart bassinet (SB) augments infant sleep and improves maternal sleep during the first 6 months post partum compared to the use of a traditional bassinet (TB). (1) Hypothesis 1a: Infants who sleep in SB will have better sleep (ie, diary and Brief Infant Sleep Questionnaire as maternally reported) [40] than those who sleep in TB. Outcomes will include maternally reported sleep duration, awakenings, as well as objectively assessed (actigraphy) wake after sleep onset and sleep onset latency. (2) Hypothesis 1b: Mothers of infants who sleep in SB will have better subjectively reported (ie, diary and Pittsburgh Sleep Quality Index) and objectively assessed (actigraphy) sleep compared to those of infants who sleep in TB. Outcomes will be the same as those for infants.Determine the effect of SB on maternal postpartum depressive and anxiety symptoms and evaluate the model that the association between SB and postpartum depressive symptoms is mediated by both infant and maternal sleep. (1) Hypothesis 2a: Mothers of infants who sleep in SB will have fewer postpartum depressive symptoms over time (ie, Edinburgh Postnatal Depression Scale) compared to those of infants who sleep in TB. (2) Hypothesis 2b: SB improves infant sleep, which then predicts better maternal sleep, and thereby predicts lower maternal depressive symptoms.Compare the trajectory of immune system function from late pregnancy through post partum between participants with and without PMADs and between SB and TB groups. (1) Hypothesis 3a: Peripheral cytokines, immune cells, and stimulated cytokine profiles of women with PMADs assessed in late pregnancy and at 3 and 6 months post partum will indicate greater innate immune activity compared to those of women without PMADs. (2) Hypothesis 3b: Mothers of infants who sleep in SB will exhibit lesser innate immune dysfunction than mothers of infants who sleep in TB.Exploratory aim: Evaluate whether the elevated risk demonstrated by previously identified PMAD epigenetic biomarkers at the TTC9B and HP1BP3 genes can be modified by using an SB. We hypothesize that the elevated risk will be reduced in the SB group compared to that in the TB group.

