#### Primary Infant Assessments

The mother will record infant sleep for 1 week per month in the baby’s day diary [46]. Boxes are filled in daily for 1 week with symbols that correspond to when the infant is asleep, awake, awake and fussy, sucking, or feeding. This measure has been widely used and exhibits desirable reliability and validity [47,48]. The Brief Infant Sleep Questionnaire [40] is used to assess the infant’s sleep during the past week. The Infant Behavior Questionnaire-Revised [49] will be used to allow mothers to report, on a 7-point scale, the frequency with which infants have enacted specific behaviors in common situations during the past week.

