#### Measures in Both Mothers and Infants

Actigraphy watches (Phillips/Respironics and ActiGraph, LLC) will be provided to the dyad each month to collect objective sleep data. Data collection and interpretation will be consistent with previous reports [59-61]. For infants, watches will be placed on the right ankle in accordance with suggested guidelines [61-63].

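### The hypothesis 2b mediation model mixes the mother's own sleep reports with actigraphy in a chain that ends in her own EPDS, so mood-coloured reporting can look like an effect of sleep on mood

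*Protocol article*

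**What the plan says.** Hypothesis 2b (protocol article, Introduction, aims) proposes a chain: the smart bassinet (SB) improves infant sleep, this improves maternal sleep, and this lowers depressive symptoms. The Mediational Analyses section states of the model that tests it: "All the outcomes of aim 1 are incorporated into the aim 2 mediational model".

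Those outcomes come from two kinds of source.

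- **Infant sleep.** Hypothesis 1a rests on "diary and Brief Infant Sleep Questionnaire as maternally reported". It continues: "Outcomes will include maternally reported sleep duration, awakenings, as well as objectively assessed (actigraphy) wake after sleep onset and sleep onset latency". Under Primary Infant Assessments: "The mother will record infant sleep for 1 week per month".
- **Maternal sleep.** Hypothesis 1b names "better subjectively reported (ie, diary and Pittsburgh Sleep Quality Index) and objectively assessed (actigraphy) sleep".
- **Actigraphy.** Under Measures in Both Mothers and Infants, the watches "will be provided to the dyad each month to collect objective sleep data".
- **End of the chain.** The EPDS, completed by the mother.

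The same section states two safeguards for the model: fit indices, and bias-corrected bootstrap intervals for non-normality. The caption of Figure 2 says that constructs may correlate within each round of the cross-lagged model. The Randomization section says that the trial is not blinded.

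**The concern.** Apart from actigraphy, one woman supplies both mediators and the outcome. In a month when her mood is low she may rate her own sleep, and her infant's, as worse than it was.

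Adjusting for last month's EPDS removes this only if the EPDS captures her mood without error. It does not, so reported sleep carries extra information about her mood and predicts next month's EPDS even if sleep does nothing to mood. Fit indices and bootstrap intervals do not detect this. Randomisation protects the link from bassinet to infant sleep, but not the two later links.

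Hypothesis 2b is the trial's mechanism claim. If the bassinet does improve infant sleep and this carries over to the mother, the first two links will hold. The claim then rests on the maternal-sleep-to-EPDS path, which is the one exposed.

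**Working it through.** The plan gives no figure to reproduce. The question is how often the full chain is declared when the true effect of sleep on mood is zero.

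**Inputs from the article.** The SB effect on infant sleep is d = 0.39 and tests are two-sided at 0.05 (Power). Recruitment is 342 (Participants) with 15% attrition, so 342 × 0.85 ≈ 291 dyads. Six monthly assessments give five month-to-month steps, so 291 × 5 = 1,455 records.

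**Assumed inputs (the article gives none of these).**
- The infant-to-maternal sleep path is 0.3.
- The month-to-month carry-over of mood is 0.6.
- EPDS reliability ρ is 0.75 to 0.85.
- Colouring λ is 0.3 to 0.5 SD of reported sleep per SD of mood.
- In the hand check, mood and true sleep have variance 1 and each sleep measure has error SD 0.6.
- All five steps are pooled, and each equation adjusts for the outcome's previous value.

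**Why the path is biased.** Let a sleep measure be R = S − λD + n, where S is true sleep, D is mood and n is error. Regress next month's EPDS on this month's EPDS and R. With no effect of sleep on mood, the coefficient of R is

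β = −0.6 λ(1 − ρ) / [1 + Var(n) + λ²(1 − ρ)].

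It is zero if ρ = 1 (no EPDS error) or λ = 0 (no colouring, as with actigraphy).

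**Hand check for an equal average of report and actigraphy.** The colouring halves to λ/2, and Var(n) = (0.36 + 0.36)/4 = 0.18. The residual variance of next month's EPDS is about 1/ρ − 0.36ρ, which is 1.063 at ρ = 0.75 and 0.870 at ρ = 0.85. The standard error is √[residual variance / (1,455 × denominator of β)]. The false rate is that of significance in the hypothesised direction, P(Z > 1.96 − z) with z = |β|/SE. Its nominal value is 2.5%.

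| ρ | λ | β | SE | z | False rate |
|---|---|---|---|---|---|
| 0.85 | 0.3 | −0.0114 | 0.0225 | 0.51 | 7% |
| 0.85 | 0.5 | −0.0189 | 0.0224 | 0.84 | 13% |
| 0.75 | 0.3 | −0.0190 | 0.0248 | 0.76 | 12% |
| 0.75 | 0.5 | −0.0314 | 0.0247 | 1.27 | 25% |

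The last figure is somewhat high because infant sleep, which carries the same colouring, is left out of this formula.

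**Simulation of the full chain** (three paths jointly significant in the hypothesised direction, dyad-clustered standard errors, 600 replicates):

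| Sleep measure | ρ 0.75, λ 0.3 | ρ 0.75, λ 0.5 | ρ 0.85, λ 0.3 | ρ 0.85, λ 0.5 |
|---|---|---|---|---|
| Equal average | 10% | 21% | 7% | 10% |
| Actigraphy only | 2%–3% | 2%–3% | 2%–3% | 2%–3% |

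Other runs of the same design, counted in either direction (nominal 5%), gave 7% to 22% for the average and 5% to 7% for actigraphy only.

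**Where the inflation shrinks.** With no EPDS error the averaged rate was about 6% in either direction, and with reports only it was also 6%. At ρ = 0.90 the averaged rate was about 8%. With colouring of 0.15 it was 5% to 7%.

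**Dependence on model structure.** A second simulation used N = 290, an EPDS error SD of 0.4 (ρ = 1/1.16 = 0.86), a single run of months without pooling, and colouring by current mood. Rates are for λ 0.3 and 0.5, in either direction.
- Lagged paths adjusted for prior EPDS: no inflation. The maternal-sleep-to-EPDS path was significant in 5% to 6%. One step has about a fifth of the records, so a small bias is rarely detected.
- Lagged paths not adjusted for prior EPDS: 7% and 19% for the average, about 2% for actigraphy only.
- All constructs from the same month: 29% and 63% for the average, 3% and 5% for actigraphy only.

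**The case against.** **Combination of measures.** The article says that aim 1 outcomes are incorporated, not that they are merged into one score. Separate constructs, parallel models or a latent factor with a method term would all fit that word, Figures 2 and 3 are not shown, and such detail may sit in a fuller document. This stands: a reader might infer a pooled score, but the text does not state one. What the text does fix is that maternal reports and actigraphy both enter a chain ending in her EPDS.

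**Reports-only rates.** With maternal reports as the only sleep measures, the same simulations give false rates of 13% to 51%, and a reader might take these as the size of the problem. The documents do not support that, because actigraphy is an aim 1 outcome for both mother and infant and so is in the model.

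**Undocumented inputs.** Reliability, colouring and carry-over are assumed, and the inflation vanishes without EPDS error, which a structural equation model could correct with a latent outcome. This stands. The low end of the averaged range is also hard to tell from actigraphy alone: with 600 replicates the Monte Carlo standard error near 5% is √(0.05 × 0.95/600) ≈ 0.9 points.

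**Event log.** The infant diary has boxes filled in daily, so it may be coloured less than a retrospective questionnaire. This is fair, and it argues for the lower part of the range.

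**Perceived sleep.** Perceived sleep may itself be a route to mood, and an actigraphy-only deciding test would drop the Pittsburgh Sleep Quality Index and the maternally reported infant duration and awakenings. This also stands. It is why the actigraphic chain should sit beside the planned model, not replace it.

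**Conclusion.** The concern holds as a possibility that the stated safeguards do not cover. If reports and actigraphy are averaged equally and the months are pooled, a chain with no true sleep-to-mood effect is declared in roughly 7% to 22% of trials, against about nominal with actigraphy alone. This rests on assumed EPDS reliability of 0.75 to 0.85 and colouring of 0.3 to 0.5 SD. With small EPDS error or weak colouring there is little or no inflation. Adjusting for prior EPDS helps but does not remove the bias while the EPDS carries error.

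Two further readings go too far. A reader might infer that the mediation result will be spurious, but the size depends on inputs and a model structure that the article does not give. A reader might also extend the point to the between-arm comparisons in aim 1, but this mechanism concerns the later links of the chain and does not bear on those comparisons.

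**What to change.** In the Mediational Analyses section:

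1. State that reported and actigraphic sleep are kept as separate constructs and are not combined into one score.
2. Prespecify, alongside the planned model, a fit of the hypothesis 2b chain with actigraphic infant and maternal sleep as mediators (for example wake after sleep onset, already an aim 1 outcome) and the EPDS as outcome, with each path adjusted for prior EPDS.
3. State that an effect of sleep itself on mood will be claimed only if the actigraphic chain agrees. If only the report-based chain is significant, describe it as an association with perceived sleep that may reflect shared reporting.

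Actigraphy is already collected monthly from both members of the dyad, so the cost is wording and one extra fit. The downside is a more cautious mechanism claim.

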**Figure 3 figure3:**

Mediational model. For diagrammatic clarity, not displayed but will be estimated as part of the model are the predictive error terms. SNOO: smart bassinet.

The cross-lagged panel model and the meditational model each will be estimated with structural equation modeling [88]. The overall adequacy of these structural equation models will be assessed using fit indices [89-91]. A nonsignificant model chi-square test is desired to signify that the model approximates the underlying data, but this index tends to be sensitive to sample size [92]. Thus, additionally interpreted will be the comparative fit index and the Tucker-Lewis index, with higher values, preferably above 0.90, indicative of a good-fitting model [93,94]. The root mean-square error of approximation is sufficiently sensitive in detecting model misspecifications and provides a 90% CI [95]. Values below 0.05 indicate close fit, between 0.05 and 0.08 fair fit, between 0.08 and 0.10 mediocre fit, and above 0.10 poor fit [95].

If the fit indices for a model would be judged satisfactory, then the magnitude of the direct paths and the *P* values of these paths will be interpreted [96]. In the mediational model, the statistical significance of these mediational processes starting from the SB intervention (vs control) to infant sleep quality to maternal sleep quality and finally to postpartum depression with be evaluated in tests of indirect effects to determine whether the mediational process is significant beyond chance [88]. As recommended for structural equation models [96], bootstrapping with bias-corrected CIs will be applied to adjust for potential nonnormality of the variables.

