**Methods:**

This study is a 6-month, parallel-arm, randomized controlled trial. Pregnant women (N=342) in the third trimester will be randomized at 1:1 ratio to use a smart bassinet (SB) or a standard commercially available bassinet (HALO BassiNest Swivel Sleeper 3.0; traditional bassinet [TB]) for up to 6 months after delivery. Participants will have their infants sleep in the bassinet, complete monthly web-based questionnaires, and record sleep data with diary and actigraphy for both the participants and their infants for 1 week each postpartum month. Blood samples will also be collected at baseline (late pregnancy) and at 3 months and 6 months post partum to assess immune functioning. The primary outcomes for this study will be postpartum mood (depressive and anxiety symptoms) and infant and maternal sleep. In addition, we are evaluating whether SB has a significant impact on immune functioning—a marker that physiologically connects sleep and mood symptoms.

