### Statistical Analysis

#### Power

Power analyses were performed using *P*<.05 (2-tailed) at .80 power, based on recommended guidelines [78-80]. The power analyses were conducted for each statistical technique to be pursued in aims 1 to 3: mixed (between-subjects and within-subjects) multivariate analysis of variance (MANOVA), mixed (between-subjects and within-subjects) analysis of variance, independent 2-sided *t* test, dependent 2-sided *t* test, correlation, and the mediational models involving structural equation modeling (based on the β coefficient). The pilot study collected similar measures from pregnant/postpartum women with a history of major depressive disorder who used SB or HALO TB. Hence, the power analyses were based on pilot sleep and mood data. Calculations revealed an average effect size across all postpartum timepoints (T1 to T6) between the treatment and control groups on the following measures: infant sleep (*d*=0.39), postpartum sleep quality (*d*=0.27), and postpartum depression (*d*=0.33). Based on these effect sizes, a sample size of 208 participants is needed for infant sleep, 434 participants for postpartum sleep quality, and 286 participants for postpartum depression to attain statistical significance. Thus, a final sample size of 393 participants will be targeted (allowing for an attrition rate of 15%).

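### The bias-corrected bootstrap test of the indirect effect (hypothesis 2b) can exceed the plan's two-sided .05 level, reaching about 10%, when exactly one link of the three-link chain is null

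*Protocol article*

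**What the plan says.** The Mediational Analyses section of the protocol article sets out the chain for hypothesis 2b as "SB versus TB→infant sleep→maternal sleep→postpartum depression". The indirect effect is therefore a product of three coefficients. The text following Figure 3 plans "tests of indirect effects to determine whether the mediational process is significant beyond chance" and then fixes the interval method: "bootstrapping with bias-corrected CIs will be applied to adjust for potential nonnormality of the variables". A cited recommendation and possible nonnormality are the only reasons given. The same text also says that the individual direct paths and their P values will be interpreted.

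The level comes from the Power section: "Power analyses were performed using *P*<.05 (2-tailed) at .80 power". The techniques listed there include the mediational models. No other level is given for hypothesis 2b. The article gives no confidence level or number of resamples for this interval, and a condensed article may leave those to a fuller document. The interval type, however, is stated.

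**The concern.** The bootstrap distribution of a product of coefficients is skewed away from zero, so more than half of the replicates tend to lie closer to zero than the estimate does. The bias correction treats this as bias and moves both limits away from zero. If one link is truly absent while the other two are real, the indirect effect is exactly zero, yet the shifted interval excludes zero too often.

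The stated reason does not require this type of interval, because the plain percentile bootstrap also makes no normality assumption.

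At stake is the mechanism claim. A plausible way for hypothesis 2b to be false is that the smart bassinet improves infant sleep, as the pilot suggests, but the gain does not carry through to maternal sleep or to mood. A borderline result in that situation could be reported as mediation because of the interval method.

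**Working it through.** **1. The level.** The Power section's effect sizes are "infant sleep (*d*=0.39), postpartum sleep quality (*d*=0.27), and postpartum depression (*d*=0.33". With n per arm = 2(1.960 + 0.842)² / d² = 15.70 / d²:

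- d=0.39: 103.2, so 104 per arm and 208 in total (plan: 208)
- d=0.27: 215.3, so 216 per arm and 432 in total (plan: 434)
- d=0.33: 144.2, so 145 per arm and 290 in total (plan: 286)

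All agree within 2%, so two-sided .05 is the level the plan works at.

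**2. Inputs for the check.**

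- Sample size: the abstract has "Pregnant women (N=342) in the third trimester will be randomized at 1:1 ratio", while the Power section targets 393 with 15% attrition. Three sizes were run: 342, 393, and 342 × 0.85 = 290.7, taken as 290.
- Path a (group to infant sleep): 0, the protocol's d=0.39, and 0.27 and 0.6 as a smaller and a larger value.
- Paths b (infant to maternal sleep) and c (maternal sleep to depression): not given in the article. Assumed, standardized, 0.14 to 0.5.
- Model: observed variables, least squares, each equation adjusted for the upstream variables, complete data. This is an assumption, since Figure 3 is not available.

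**3. Intervals.** The estimate is a × b × c. The percentile interval takes the 2.5% and 97.5% quantiles of the bootstrap replicates. The bias-corrected (BC) interval takes the quantiles Φ(2z₀ ± 1.96), where z₀ = Φ⁻¹(share of replicates below the estimate). Each setting had 8,000 simulated trials with 1,000 resamples each, for a simulation standard error of about 0.3 points.

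**4. Rejection of a true null, BC / percentile, in %.**

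| a, b, c | N=290 | N=342 | N=393 |
|---|---|---|---|
| 0, 0.14, 0.14 | 6.4 / 1.4 | 6.7 / 1.9 | 8.0 / 2.3 |
| 0, 0.2, 0.2 | 9.6 / 3.8 | 9.2 / 4.1 | 9.3 / 4.6 |
| 0, 0.3, 0.3 | 8.8 / 5.2 | 7.7 / 4.9 | 7.6 / 5.1 |
| 0, 0.3, 0.5 | 7.6 / 5.3 | 6.8 / 4.9 | 6.8 / 5.1 |
| 0, 0.5, 0.5 | 6.7 / 5.3 | 5.9 / 4.9 | 5.9 / 5.1 |
| 0.39, 0, 0.3 | 9.3 / 4.6 | 9.2 / 4.7 | 9.0 / 5.2 |
| 0.39, 0, 0.5 | 8.2 / 4.6 | 8.4 / 4.7 | 8.3 / 5.2 |
| 0.39, 0.3, 0 | 9.1 / 5.0 | 9.7 / 5.3 | 8.7 / 5.2 |
| 0.39, 0.5, 0 | 8.2 / 5.0 | 8.9 / 5.3 | 8.2 / 5.2 |
| 0.27, 0.3, 0 | 7.4 / 3.0 | 8.0 / 3.3 | 7.7 / 3.6 |
| 0.6, 0.5, 0 | 8.1 / 5.8 | 7.9 / 5.9 | 7.2 / 5.5 |
| *Two or three links null* | | | |
| 0, 0, 0.5 | 0.7 / 0.1 | 0.5 / 0.1 | 0.7 / 0.2 |
| 0.39, 0, 0 | 0.8 / 0.1 | 0.9 / 0.1 | 1.0 / 0.2 |
| 0, 0, 0 | 0.1 / 0.0 | 0.1 / 0.0 | 0.1 / 0.0 |

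**5. Nonnormality.** With skewed errors at N=342, BC rejected in 7.6% (0, 0.3, 0.3), 6.2% (0, 0.5, 0.5) and 9.7% (0.39, 0.3, 0). The percentile interval gave 5.1%, 5.2% and 5.5%. Skewness neither causes nor cures the excess.

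**6. Power given up.** At N=342 with d=0.39, moving from BC to percentile lowers the chance of declaring true mediation from about 97% to 95% when both later paths are 0.3, and from about 93% to 86% when both are 0.2.

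**The case against.** The strongest case is that the inflation is not a general property of this test. The null for a three-path product includes cases with two or three absent links, and there the interval is far below 5%. Even with one absent link, the rate is only about 6-7% when the bassinet has no effect and both later paths are strong. This stands, and the point is limited accordingly. It does not remove the concern: a level has to hold over the whole null, and conservatism in some cases does not offset rejection near 10% in others.

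The simulated model is also simpler than the plan, which is a longitudinal structural equation model using all aim 1 outcomes, with provision for missing data. The later path sizes are assumptions. This stands too: the direction should carry over, but the exact percentages are not established for the final model.

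The protocol also interprets the P values of the individual paths, which would alert a careful reader to a weak link. But it does not require all three paths to be significant before mediation is declared, so the level is not restored.

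Finally, the bias-corrected interval has more power, and the percentile interval is not exact either (1.4-5.9% with one null link). Both are true, but the percentile excess is at most about 1 point.

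**Conclusion.** The concern holds conditionally. With exactly one null link and the other two present, the bias-corrected test rejects in about 6-10% of trials against the plan's two-sided .05 level, and in 8-10% when the bassinet effect is d=0.39 and a later link is absent. The percentile bootstrap stays at about 5% or less in most of these settings. The conclusion changes little across the three sample sizes. It rests on the assumed later paths and on the observed-variable serial model.

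Three stronger readings are tempting, and the documents do not support them:

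- A reader might infer that any true null is rejected in 7-10% of trials. With two or more null links the rate is about 1% or less.
- A reader might infer that the protocol states a 5% error rate for this interval and misses it. The .05 is the general level in the Power section, and no error rate is attached to the interval.
- A reader might infer that the trial's main comparisons are at risk. Hypotheses 1a, 1b and 2a do not use this interval, and only the mediation claim in 2b is affected.

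**What to change.** In the Mediational Analyses section, in the text after Figure 3, name the 95% percentile bootstrap interval as the test of the indirect effect, and report bias-corrected intervals only as a sensitivity analysis. The nonnormality reason can stay, since the percentile interval meets it equally well.

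This costs one phrase, one software option and the modest power loss shown in step 6. Analysis is expected to finish by July 2028, so the change can be recorded before results are known.
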